### Laboratory measurements

The following laboratory measurements will be recorded on the same day: HbA1c (agarose electrophoresis; normal value <6%; Hyrys Hydrasys, Sebia, France); serum total cholesterol, HDL cholesterol, and triglycerides (enzymatic colorimetry; Hitachi 912; Roche Diagnostic); creatinine (colorimetry; Kone Optima; Thermolab Systems, Helsinki, Finland); and urinary albumin excretion rate on a 24-h urine collection (laser immunonephelometry; BN100; Dade-Behring, Paris, France). LDL cholesterol will be calculated according to the Friedwald formula and creatinine clearance according to the Cockroft and Gault formula.

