**Methods/Design:**

The study will enroll 600 patients with type 2 diabetes who have angiographically normal ventricular function and coronary arteries. The goal of the MASS IV-DM Trial is to achieve a long-term evaluation of the development of coronary atherosclerosis by using angiograms and coronary-artery calcium scan by electron-beam computed tomography at baseline and after 5 years of follow-up. In addition, the incidence of major cardiovascular events, the dysfunction of various organs involved in this disease, particularly microalbuminuria and renal function, will be analyzed through clinical evaluation. In addition, an effort will be made to investigate in depth the presence of major cardiovascular risk factors, especially the biochemical profile, metabolic syndrome inflammatory activity, oxidative stress, endothelial function, prothrombotic factors, and profibrinolytic and platelet activity. An evaluation will be made of the polymorphism as a determinant of disease and its possible role in the genesis of micro- and macrovascular damage.

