## Background

Diabetes mellitus is a potentially serious disease and is currently the major concern of public health officials. This disease has a prevalence of 2% to 5% in most Western countries and has grown exponentially around the world, possibly because of changing dietary habits in recent years [1-3].

Patients with type 2 diabetes often have cardiovascular risk factors that may further influence the prognosis of the disease. These risk factors compose metabolic syndrome. They include high blood pressure [4,5], dyslipidemia, and obesity, which have been reported as participating in the pathogenesis of cardiovascular events by possible action on coronary endothelial function [5]. Moreover, the high rate of urinary albumin excretion has been hypothesized as an additional indicator of endothelial dysfunction, which is associated with a higher rate of renal and cardiovascular events [6]. Other risk factors include potential age and sex [7], smoking [8], glycemic control, lipids [5,9], and hormone replacement therapies [10].

Major studies have shown that healthy endothelium inhibits adhesion of platelets and leukocytes to the vessel surface and maintains the balance of profibrinolytic and prothrombotic activity [11]. However, with the occurrence of dysfunction, the endothelium is a potential contributor to the pathogenesis of vascular disease in diabetes mellitus and atherosclerosis [12].

Under physiological conditions, there is a delicate and balanced release of relaxing factors and endothelium-derived contraction factors that apparently is imbalanced in diabetes and may contribute to the development of atherosclerosis, thus contributing to the further progression of vascular injury in different organs [13].

Hyperglycemia has been implicated as the main causal factor in the development of coronary atherosclerosis in diabetic patients. However, the mechanisms associated with this disorder are likely to be multifactorial. Among these are hypertension, abdominal obesity, and pluri-metabolic syndrome [14-16].

Besides these, we highlight the presence of decreased high-density lipoprotein and elevated low-density lipoprotein (LDL) cholesterol, high triglycerides, increased VLDL, nephropathy, altered coagulation, and platelet dysfunction. Insulin resistance, another existing condition in diabetes, has been described as responsible for the increased risk of death from coronary artery disease (CAD) [15-17].

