The objectives of the MASS IV-DM Trial is to compare the clinical data, laboratory profile, and angiographic evolution at baseline with that at 5-year follow-up in patients with type 2 diabetes who have angiographically normal coronary arteries.

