## Methods/Design

The MASS IV-DM Trial is an institutional project to be conducted at the Heart Institute (InCor), Hospital das Clinicas, University of São Paulo, and is designed to prospectively investigate 600 type 2 diabetic patients with a clinical suspicion of coronary insufficiency and electrocardiographic evidence of myocardial ischemia who have normal coronary angiographies and ventricular function.

It is designed as a secondary prospective cohort study. Only patients with angiographically normal coronary arteries (by semi quantitative TCA equal to zero) will be included in the study. After inclusion, all patients will undergo a 320-row multidetector computed tomography (MDCT) angiography of the coronary arteries to assess the calcium score as well as the plaque characteristics if present any. Both angiography studies will be repeated after 5 years of follow-up. Ischemia induced by stress electrocardiography and associated with myocardial nuclear scintigraphy will be performed at the beginning and end of the study. Furthermore, ventricular function will be measured by echocardiography at baseline, and vascular reactivity and endothelial function will be recorded at the beginning and end of the study. Laboratory tests will include a biochemical profile of blood lipids, renal function, urinalysis, genetic polymorphism, oxidative stress, and inflammatory activity, among others. All patients will undergo an outpatient clinical evaluation every 6 months. The schedule of activities is shown in Table 1.

**Table 1 T1:** Schedule of measurements.

	S	6	12	18	24	30	36	42	48	54	60
		m	m	m	m	m	m	m	m	m	m
History/events	X	X	X	X	X	X	X	X	X	X	X
Physical examination	X		X		X		X		X		X
Symptom assessment	X	X	X	X	X	X	X	X	X	X	X
Routine laboratory	X	X	X		X		X		X		X
Electrocardiography	X	X	X		X		X		X		X
Echocardiography	X		X		X		X		X		X
Stress MPI	X						X				X
Medications	X	X	X	X	X	X	X	X	X	X	X
Angiograms	X										X
CAC-Scan	X										X
Arterial stiffness	X										X
Resources utilization											X
Quality of life	X										X
Work status	X										X
Serious adverse events			Continuous								X

Abbreviations: S = baseline; 6m = 6 month after study entry; 12 m to 60 m denotes months after study entry. Stress MPI=Stress myocardial perfusion imaging, CAC-Scan=Coronary-artery calcium (CAC) scan

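### The only calculated renal function measure, Cockcroft-Gault clearance, is proportional to body weight, so weight change over 5 years is partly read as renal change

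*Protocol article*

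**What the plan says.** Four parts of the protocol article bear on this point.

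- **Measure.** The Laboratory measurements section assays serum creatinine, measures "urinary albumin excretion rate on a 24-h urine collection", and calculates "creatinine clearance according to the Cockroft and Gault formula". It names no other calculated renal function measure. It does not say which body weight enters the formula or whether the result is indexed to body size.
- **Use.** The abstract (Methods/Design) states that "the dysfunction of various organs involved in this disease, particularly microalbuminuria and renal function, will be analyzed through clinical evaluation". The Methods/Design section of the main text puts renal function in the laboratory panel: "Laboratory tests will include a biochemical profile of blood lipids, renal function, urinalysis, genetic polymorphism, oxidative stress, and inflammatory activity, among others".
- **Comparison over time.** The objective at the end of the Background is to "compare the clinical data, laboratory profile, and angiographic evolution at baseline with that at 5-year follow-up".
- **Risk factors.** The Background lists the components of metabolic syndrome: "They include high blood pressure [4,5], dyslipidemia, and obesity". The abstract puts metabolic syndrome among the factors to be investigated in depth: "especially the biochemical profile, metabolic syndrome inflammatory activity, oxidative stress".

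**The concern.** A measure used to follow renal function within a patient should move when renal function moves and stay still otherwise. Cockcroft-Gault has weight as a straight multiplier. If a patient's weight changes over 5 years while creatinine does not, the calculated clearance changes anyway. If weight and creatinine rise by the same percentage, the weight term hides the rise in creatinine.

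The same feature affects comparisons between patients. Obesity and metabolic syndrome are factors of interest in this cohort. Weight both defines obesity and enters the numerator of the renal measure. At equal age, sex and creatinine, the heavier patient always scores higher. A comparison of calculated clearance across obesity or metabolic syndrome groups would start with that tilt.

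What is at stake is how 5-year change in calculated clearance is interpreted, and how clearance is compared by body size. The angiographic and event aims do not depend on it.

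**Working it through.** The article gives no renal figure, effect size or weight data, so there is no stated number to reproduce. The check evaluates the named formula directly.

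**Formula.** The article names it but does not print it. In its standard form:

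CrCl (mL/min) = (140 − age) × weight (kg) / (72 × serum creatinine in mg/dL), × 0.85 in women.

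**Assumed inputs (none from the article).** A man with creatinine 1.0 mg/dL, weight 80 kg at age 60, followed to age 65. The formula uses actual body weight and the result is not indexed, which is the ordinary reading.

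**Step 1: proportionality.** At fixed age, sex and creatinine, the ratio of two estimates is the ratio of the two weights. A weight change of ±5%, ±10% or ±15% changes the estimate by ±5%, ±10% or ±15%. This percentage does not depend on the inputs chosen. At 80 kg and age 60 it equals ±4.4, ±8.9 or ±13.3 mL/min.

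**Step 2: same man, same creatinine, three weights at 65.**

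| Weight at 65 | Calculation | CrCl (mL/min) |
|---|---|---|
| 75 kg | 75 × 75 / 72 | 78.1 |
| 80 kg | 75 × 80 / 72 | 83.3 |
| 85 kg | 75 × 85 / 72 | 88.5 |

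The spread is 88.5 − 78.1 = 10.4 mL/min, from weight alone. At age 60 and 80 kg he scored 80 × 80 / 72 = 88.9. With a 5 kg gain his clearance looks unchanged. With a 5 kg loss it falls by 88.9 − 78.1 = 10.8 mL/min. Creatinine is identical in both cases.

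**Step 3: masking.** If weight and creatinine both rise by 10%, the factor is 1.10 / 1.10 = 1. At fixed age the estimate does not register the rise in creatinine.

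**Step 4: between patients, age 60, creatinine 1.0 mg/dL.** 70 kg gives 80 × 70 / 72 = 77.8; 100 kg gives 80 × 100 / 72 = 111.1; 110 kg gives 80 × 110 / 72 = 122.2 mL/min. From 70 to 100 kg the difference is 100 / 70 − 1 = 43%.

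**Step 5: would indexing be enough?** With the DuBois surface-area formula (weight exponent 0.425), the indexed estimate still varies as weight to the power 1 − 0.425 = 0.575. A 10% gain gives 1.10^0.575 − 1 = 5.6%, and 70 against 100 kg gives (100 / 70)^0.575 − 1 = 22.8%. Indexing about halves the dependence and does not remove it.

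**Step 6: an equation without a weight term.** With creatinine unchanged, weight change alone moves the estimate by 0%.

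**The case against.** The best case for the plan has five parts.

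1. **Clearance is not named as an endpoint.** It is one derived value in a laboratory list. Serum creatinine and 24-hour albumin excretion, which contain no weight term, are recorded too. This stands and limits the reach of the point. It does not remove it, because renal function is to be analysed, the laboratory profile is compared over 5 years, and this is the only calculated measure of renal function named.
2. **Part of the weight effect can be real.** Unindexed clearance is an absolute quantity, and larger people can have more of it. If gained weight includes muscle, creatinine production rises, and a stable serum creatinine can go with a true rise in clearance. This stands. A reader might take the whole 10.4 mL/min, or the whole gap between 70 and 110 kg, as artefact, but nothing in the article supports that.
3. **No affected analysis is specified.** The Statistical analyses section mentions neither clearance nor a regression of renal function on obesity. Its paired t test is assigned to hemodynamic parameters. A reader might infer a biased obesity–renal regression or a high chance of a falsely significant change, but the article assigns no such analysis and gives no standard deviation from which to calculate that chance. The tilt would apply to such a comparison if it were made.
4. **The main aim is vascular.** A reader might link the tilt to the search for a protective mechanism. The Background ties that mechanism to vascular involvement and cardiovascular events, not to renal function, so the link does not hold.
5. **Details may sit elsewhere.** The type of weight, indexing or adjustment for weight may be in a full protocol or analysis plan that is not shown. Their absence from the article is therefore not the criticism. The criticism is of the formula that the article does name.

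The formula also falls with age. That is no reason to prefer another equation here, because the replacement contains age as well.

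**Conclusion.** The concern holds in a limited form. The article fixes a weight-proportional estimate as its only calculated renal function measure in a cohort compared over 5 years, with obesity among the factors of interest. At fixed age and creatinine, a given percentage change in weight produces the same percentage change in calculated clearance. In the illustration, 75 against 85 kg at age 65 gives 78.1 against 88.5 mL/min.

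The result rests on the standard formula, actual body weight and no indexing. The patient values are assumed, and the article gives no weight data from which to judge how large weight changes will be in this cohort. It does not show that the plan's whole renal assessment is invalid: creatinine and albumin excretion are unaffected, and some of the weight dependence may be physiological. The change is worth making because it is a better method at almost no cost, but it is secondary to the angiographic and event aims.

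**What to change.** In the Laboratory measurements section, name a creatinine-based GFR equation without a weight term (for example CKD-EPI) as the calculated measure of renal function and of its change from baseline to 5 years. Keep Cockcroft-Gault clearance as a descriptive value.

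**Cost.** There is no new sample, visit or assay. The equation needs creatinine, age and sex, all of which Cockcroft-Gault already requires, and it can be calculated from the same blood result at each laboratory visit. The one drawback is that the weight-free estimate is expressed per standard body surface area, so it is not directly comparable with earlier Cockcroft-Gault series. Keeping the descriptive value covers that. Indexing Cockcroft-Gault to body surface area is not an adequate substitute, for the reason shown in step 5.

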### Genetic Analysis

All patients will have genomic DNA extracted from whole blood at study enrollment. Genomic DNA will be extracted following a standard salting-out protocol. Assuming that genetic factors will be responsible, at least in part, for different outcomes of diabetic patients regarding coronary artery disease progression, we plan to use this resource for genetic risk stratification of the studied individuals. Initially, our protocol will follow previously described *loci *associated with different intermediate phenotypes of coronary artery disease pathology (ie, lipid levels, diabetes, atherosclerosis phenotypes, hypertension/blood pressure), hypothesizing that they will also modulate the risk of coronary disease progression in this particular cohort.

### Statistical analyses

All data will be expressed as means ± SD. Differences between the data of patients for clinical and biological characteristics and basal hemodynamic parameters were analyzed by the nonparametric Mann-Whitney test. Changes in hemodynamic parameters at baseline and the end of follow-up will be analyzed with the paired Student *t *test. Comparisons between coronary artery dimensions at baseline and the end of the study will be made by 2-way ANOVA with repeated measures for experimental condition factor followed by the Fisher protected least-significance difference test.

The Spearman test will be used to find the correlates of coronary endothelium-dependent vasoreactivity. Due to its skewed distribution, urinary albumin excretion rate will be log transformed in the correlation analyses. A backward linear multiple regression will be performed to find the independent predictors for endothelium-dependent coronary vasoreactivity. Statistical significance is assumed when P < 0.05.

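### Urinary albumin excretion is declared skewed, yet the blanket mean ± SD rule leaves its baseline and 5-year summaries on the raw scale (minor)

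*Protocol article*

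**What the plan says.** All of the plan's statements on scale are in the Statistical analyses section of the protocol article.

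- Summary rule, with no exception named: "All data will be expressed as means ± SD".
- On albumin excretion: "Due to its skewed distribution, urinary albumin excretion rate will be log transformed in the correlation analyses".
- Correlation method: "The Spearman test will be used to find the correlates of coronary endothelium-dependent vasoreactivity".
- The paired t test is assigned to one class of variable: "Changes in hemodynamic parameters at baseline and the end of follow-up will be analyzed". Neither that section nor any other names a test for the 5-year change in albumin excretion.

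Elsewhere, the Abstract (Methods/Design) lists among the outcomes "the dysfunction of various organs involved in this disease, particularly microalbuminuria and renal function, will be analyzed through clinical evaluation". The objectives paragraph that closes the Background sets out to "compare the clinical data, laboratory profile, and angiographic evolution at baseline with that at 5-year follow-up". The Laboratory measurements section records albumin excretion as a continuous rate from a 24-hour urine collection. The article mentions no median, quartiles, geometric mean or log-scale summary for this variable.

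**The concern.** The plan recognises that albumin excretion is skewed, applies a remedy in one place, and then fixes a summary for all data that ignores the skew. The two visit summaries, and any difference read from them, belong to a stated objective. For a strongly right-skewed variable the raw mean sits well above the typical patient. The SD can exceed the mean, which implies impossible negative values one SD below it. A handful of patients with heavy albuminuria can also move the cohort figure. At stake is how representative the reported level and 5-year change in albumin excretion are, for one outcome among several.

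**Working it through.** **Inputs from the article.** The mean ± SD rule for all data; the declared skew; the log restricted to correlation analyses; Spearman as the correlation method; a continuous 24-hour rate; 600 patients. The article gives no mean, SD, quantile or expected change for albumin excretion, so it has no figure to reproduce.

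**Step 1: the statements side by side.** The summary rule covers all data. Albumin excretion at baseline and at 5 years is part of those data. The log exception reaches only the correlation analyses. Both visit summaries therefore stay on the raw scale, for a variable that the same section calls skewed.

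**Step 2: what the stated log does.** Spearman's coefficient depends only on ranks. The log is strictly increasing, so it leaves ranks, and hence the coefficient, unchanged. In a simulated log-normal sample of 600 the coefficient was −0.272 on both raw and log values. The log can matter only in the planned linear regression, and only if that counts as a correlation analysis.

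**Step 3: illustration of size.** Assumption, not from the article: albumin excretion is log-normal with log-scale SD s. Then:

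- mean/median = exp(s²/2)
- SD/mean = √(exp(s²) − 1)
- share of patients below the mean = Φ(s/2)
- share of the total held by the top 5% of patients = 1 − Φ(1.645 − s)

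For s = 1.0: exp(0.5) = 1.65; √(2.718 − 1) = 1.31; Φ(0.5) = 69%; 1 − Φ(0.645) = 26%.

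For s = 1.5: exp(1.125) = 3.08; √(9.488 − 1) = 2.91; Φ(0.75) = 77%; 1 − Φ(0.145) = 44%.

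| s | mean/median | SD/mean | below the mean | held by top 5% |
|---|---|---|---|---|
| 0.8 | 1.38 | 0.95 | 66% | 20% |
| 1.0 | 1.65 | 1.31 | 69% | 26% |
| 1.2 | 2.05 | 1.79 | 73% | 33% |
| 1.5 | 3.08 | 2.91 | 77% | 44% |

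The top 5% of 600 is 0.05 × 600 = 30 patients. Mean minus one SD, in units of the mean, is 1 − 0.95 = 0.05 at s = 0.8, 1 − 1.31 = −0.31 at s = 1.0 and 1 − 2.91 = −1.91 at s = 1.5. The summary thus implies negative excretion from s = 1.0 upward in this table, and is only just positive at the mildest skew shown.

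**The case against.** **The rule is only a convention.** Taken literally it would also cover clinical events and work status, which cannot be given as mean ± SD, so it was probably not meant for every variable. This is a journal article, and tabulation of individual laboratory variables is commonly left to the analysis plan. That stands, and it keeps the point minor. It does not remove it: the article is not silent but states a universal rule that conflicts with its own description of one variable.

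**Much of the planned inference does not depend on scale.** The Mann-Whitney test for differences between patients and the Spearman test are rank-based. That stands, and neither is criticised here.

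**Microalbuminuria may be handled as a category.** If so, the point reaches only the continuous rate. The article defines no categories and measures a rate, so the point remains for that rate.

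**Stronger readings.** A reader might infer that the 5-year change in albumin excretion will be tested by a raw-scale paired t test with reduced power. The article assigns that test to hemodynamic parameters only. A reader might also infer that a general shift toward microalbuminuria would go undetected. That depends on the size and pattern of the change and on the correlation between visits, none of which the article gives; a large enough shift shows on either scale. Nor can the point be extended to the calcium score: the article says nothing about its distribution, so its skew would be the reviewer's assumption rather than the plan's own statement.

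**Conclusion.** The inconsistency is real and minor. The plan declares albumin excretion skewed, limits the log to analyses where the named rank test does not need it, and by its blanket rule leaves the baseline and 5-year summaries of a singled-out outcome on the raw scale. That much rests on the text alone. The size does not: a mean of 1.65 to 3.08 times the median, an SD of 1.31 to 2.91 times the mean and a top-5% share of about 26% to 44% hold only for an assumed log-normal distribution with log-scale SD 1.0 to 1.5, and the effect is smaller at milder skew. No stated figure is wrong and no named test is shown to be invalid. The point concerns how albumin excretion is summarised and how its change is reported.

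**What to change.** In the Statistical analyses section:

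- Limit mean ± SD to continuous variables that are roughly symmetric.
- Report urinary albumin excretion rate at each visit as a geometric mean, or as median and quartiles.
- Report its 5-year change as the mean paired difference in log values, back-transformed to a ratio with 95% CI.

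This extends a scale that the plan already accepts for this variable. It costs one or two sentences and needs no new data, visits or patients. The downside is that readers see a ratio of geometric means rather than a mean difference in the original units.

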### Patients

Diabetic patients with clinically suspected (based on presence of the CCS II/III angina) or documented myocardial ischemia based on ET will undergo coronary angiography that will be performed according to the technique of Sones or Seldinger. For the evaluation of ventricular function, patients will receive contrast in the left ventricle, and measures will be taken with the patient in the right anterior oblique position. The calculation of left ventricular ejection fraction will be made according to the Dodge formula.

For the angiographic study of the coronary arteries, 5 views of the left coronary artery and 2 of the right coronary artery will be obtained. These effects allow a clear assessment of each coronary artery, thus forming 4 pairs of perpendicular incidence suitable for biplane analysis.

Nitrates or other vasoactive drugs will be available when needed. The same sequence of arteriographic projections, field X-ray, and size of catheters will be followed in each patient and similarly in subsequent examinations. These conditions will be crucial for the accurate assessment of the artery after 5 years of follow-up.

Possible changes in the lumen of the coronary arteries will be assessed visually and quantitatively. Two experienced observers are blinded to the identity of the patient during both tests and also for the sequence of films at the beginning and end of the study.

The pair of films, the initial and final will be seen both side by side with 5 times magnification in a projector system adapted for this analysis.

To evaluate the second angiogram, 2 incidences will be selected of a good quality at the same point in the cardiac cycle as on the first angiogram of each coronary artery studied. Based on direct visual comparison of the coronary arteries, by consensus, the arteries will be rated as unchanged, definitely changed, or possibly changed. For possibly changed, a third frame will be selected for each view from each film.

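### The repeated-measures ANOVA for coronary dimensions names a factor this cohort does not have and leaves its second factor and unit of analysis undefined; if arteries are analysed singly, the test of 5-year change is anti-conservative

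*Protocol article*

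**What the plan says.** The Statistical analyses section of the protocol article gives one method for the dimensions. It says that their comparison between the first and the 5-year angiogram "will be made by 2-way ANOVA with repeated measures for experimental condition factor followed by the Fisher protected least-significance difference test". The threshold is "Statistical significance is assumed when P < 0.05", with sidedness not stated.

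The Methods/Design section describes one cohort, "designed to prospectively investigate 600 type 2 diabetic patients", with no randomised or comparison arm. The Patients section shows that each patient contributes more than one artery: "5 views of the left coronary artery and 2 of the right coronary artery will be obtained". Reading is also by artery. Frames for the second angiogram are chosen "at the same point in the cardiac cycle as on the first angiogram of each coronary artery studied", and "by consensus, the arteries will be rated as unchanged, definitely changed, or possibly changed". The same section says that lumen changes will be assessed quantitatively as well as visually.

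Nothing in the article says that dimensions are averaged per patient, that arteries are analysed one at a time, or that the model contains a patient effect.

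**The concern.** A two-way ANOVA with one repeated factor has two factors and one kind of subject. Here the repeated factor is called experimental condition, which has no referent in an observational single cohort. The only repeated contrast the sentence supplies is baseline against 5 years. The second factor is missing, and so is the subject.

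Artery is a natural candidate for that second factor. The reading is by artery and no patient groups are defined for this test. The preceding sentence also uses a paired t test for the same two time points in hemodynamic parameters, which suggests that coronary dimensions carry an extra factor. If artery is the second factor and is not repeated, each artery becomes its own subject. Arteries of one patient share systemic risk factors, treatment and imaging session, so their changes are likely to be positively correlated. An analysis that ignores this uses too small an error term for the overall 5-year change.

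The article's abstract makes the long-term development of coronary atherosclerosis, by angiogram and calcium scan, the goal of the study. This ANOVA is the only test the article names for coronary dimensions, although it does not call it primary.

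**Working it through.** **No figure to reproduce.** The article gives no power calculation, effect size, standard deviation or within-patient correlation, so the check is of the consequence if artery-level values are analysed.

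**Inputs from the protocol article:** 600 patients; two time points; nominal level 0.05 (taken as two-sided); at least the left and right coronary arteries in each patient.

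**Assumed inputs:** number of arteries per patient, m = 2 or 3; correlation of 5-year change between arteries of one patient, ρ = 0 to 0.5.

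**Formula.** Let DE = 1 + (m − 1)ρ. If arteries are treated as independent, the variance of the mean change is understated by the factor DE, and the true two-sided type I error is 2 × [1 − Φ(1.96/√DE)].

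Example, m = 3 and ρ = 0.3: DE = 1 + 2 × 0.3 = 1.6; 1.96/√1.6 = 1.55; true error = 0.121.

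Example, m = 2 and ρ = 0.5: DE = 1 + 1 × 0.5 = 1.5; 1.96/√1.5 = 1.60; true error = 0.110.

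| ρ | m = 2: DE | m = 2: true error | m = 3: DE | m = 3: true error |
|---|---|---|---|---|
| 0 | 1.0 | 0.050 | 1.0 | 0.050 |
| 0.1 | 1.1 | 0.062 | 1.2 | 0.074 |
| 0.3 | 1.3 | 0.086 | 1.6 | 0.121 |
| 0.5 | 1.5 | 0.110 | 2.0 | 0.166 |

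With 3 arteries, the nominal 600 × 3 = 1800 arteries carry the information of 1800/DE = 1500, 1125 and 900 independent ones at ρ = 0.1, 0.3 and 0.5.

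**Simulation under no change** (600 patients, 3 arteries, 4000 runs; time repeated, artery as a non-repeated factor):

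| ρ | Time effect | Artery-by-time | Test on patient-mean change |
|---|---|---|---|
| 0 | 0.051 | 0.055 | 0.051 |
| 0.1 | 0.079 | 0.038 | 0.051 |
| 0.3 | 0.122 | 0.013 | 0.050 |
| 0.5 | 0.171 | 0.002 | 0.047 |

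The simulated time effect agrees with the formula. The artery-by-time test errs the other way: differences between arteries of one patient vary less than the pooled error assumes, so that test becomes conservative. Taking one value per patient restores the nominal level.

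**The case against.** The strongest reply is that the article never says artery is a factor, still less a between-subject one. Other readings exist. The Mann-Whitney comparison in the same section needs two patient groups. The Background expects some patients to progress and others not, and the Genetic Analysis section plans risk stratification. A group-by-time ANOVA with time repeated is a standard design, and with one value per patient it has no clustering problem. Experimental condition might also refer to the vasoreactivity work mentioned a few lines later. The artery-level rating is a visual category, whereas the ANOVA is on dimensions. And a condensed article may leave the unit of analysis to a fuller document.

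Much of this stands. A reader might infer that the plan does treat arteries as independent and that its evidence for change is therefore inflated. The documents do not support that as a statement of fact, because the second factor and the unit are not given.

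The reply does not remove the point. The sentence is not silent: it fixes a model and declares repeated measures for a factor the cohort lacks. A patient grouping would not by itself solve the problem, since a group-by-time ANOVA has no place for artery and several arteries per patient would still enter unclustered unless they were first reduced to one value or analysed separately. If experimental condition means a vasoreactivity condition and time is the other factor, then time is the factor not declared repeated, although each patient has both angiograms.

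Three further inferences should be resisted:
- **The least-significant-difference comparisons inherit the inflation.** This is not shown. A baseline to 5-year contrast within one artery uses one change per patient, so clustering does not understate its variance.
- **The inflation is much larger because many coronary segments are measured.** The article describes no coronary segments for the angiographic reading; its 17-segment model belongs to perfusion imaging.
- **The visual rating has the same fault.** The Statistical analyses section states no test for that rating.

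**Conclusion.** The concern holds conditionally. The article specifies an ANOVA whose only named factor does not exist in this cohort and whose second factor and unit of analysis are undefined, while several arteries are measured in each patient. If artery-level dimensions enter that model, the test of overall 5-year change is anti-conservative: about 0.06 to 0.11 with 2 arteries and 0.07 to 0.17 with 3, instead of 0.05, for correlations of 0.1 to 0.5. Intervals for the change would be too narrow by a factor √DE, that is 1.05 to 1.22 with 2 arteries and 1.10 to 1.41 with 3.

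These sizes rest on an assumed number of arteries, an assumed positive correlation of changes and a two-sided test. Because the direction of error depends on the test, no general statement that the analysis is too liberal is justified.

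**What to change.** Replace the ANOVA sentence in the Statistical analyses section, for example with:

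*Coronary dimensions will be analysed by a linear mixed model with fixed effects of time (baseline, 5 years), artery and time-by-artery, both factors being within patient. The model will include a patient random effect for level and for change over time, and an artery-within-patient random effect. Any patient grouping will enter as a named between-patient factor. The 5-year change will be reported as the time contrast with its 95% confidence interval.*

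A simpler alternative is to average the change over arteries within each patient and test the per-patient mean change, again with its 95% confidence interval. Either way the patient becomes the independent unit, and the undefined experimental-condition factor disappears.

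No new data are needed. The cost is a few sentences, slightly more analysis work and possibly wider intervals for the angiographic change. If the intention was already one value per patient, saying so and naming the two factors would settle the point.
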